## Ascertainment of comorbidities and antithrombotic treatment

Comorbidities needed to calculate the CHADS2 score and other cerebrovascular risk factors will be noted. Nurses will search the medical record from January 1, 2004 onwards to allow ascertainment of medical history available at the time of randomisation.

Nurses will record antithrombotic treatments and dates of noted use. Dates and results of international normalised ratio (INR) testing and recorded suspensions of anticoagulation, if prescribed, are also noted. These data were collected to enable ascertainment of antithrombotic use current at randomisation and outcome assessment during the 12-month period after randomisation (see below).

## Cerebrovascular and bleeding events

All entries of cerebrovascular and bleeding events or episodes noted in the medical record from January 1, 2004 will be recorded so that the history of these events current at the time of randomisation and new events occurring during the 12 months after the date of randomisation will be recorded (see below).

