Studies suggest that strategies to improve the management of NVAF should address physicians' concerns about the risks of anticoagulation. Choudhry *et al*. [14] reported that physicians were less likely to prescribe warfarin for patients with NVAF after any one of their patients receiving warfarin was admitted to a hospital for a haemorrhage. Physicians were no more or less likely to prescribe warfarin, however, if any one of their patients with NVAF had been admitted to a hospital with an ischaemic stroke.

In our representative survey of 596 Australian primarycare physicians, known in Australia as general practitioners (GPs), the GPs appeared overly cautious in prescribing anticoagulation in the presence of any perceived risk of major and even minor bleeding, even where treatment benefits clearly outweighed the risk of harm [15,16]. A substantial proportion of GPs 'strongly agreed' or 'agreed' that they were 'often unsure whether or not to prescribe warfarin' and that 'it is hard to decide whether the benefits of warfarin outweigh the risks or vice versa' (30.0% and 38.4%, respectively). Other local surveys have indicated GP reluctance to prescribe anticoagulation for NVAF in the elderly or in the presence of perceived bleeding risks, which would not necessarily preclude anticoagulation on the available evidence [17,18].

Clinicians with perceived specialist knowledge in stroke prevention and atrial fibrillation may be effective educators and preceptors for improving clinical management of NVAF. Yet, such access to experts in stroke medicine seems limited. In our national survey, a significant proportion of Australian GPs were either 'dissatisfied' or 'very dissatisfied' with access to neurologists (51.8%), even in metropolitan settings (47.4%) ([name], [name], [name], unpublished data). Previous research has found that collaborative involvement of specialists with family physicians increases anticoagulation prescribing in patients, suggesting collaboration with specialists is an important factor in patient care [19].

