### Baseline comparisons between DESPATCH intervention and control groups

We will compare groups on key patient and practice characteristics current on the date of randomisation. Specifically, we will compare the DESPATCH and control groups on the numbers of patients identified with atrial fibrillation, patient sex, age (mean and median differences), CHADS2 scores (0, 1, 2+, and mean scores), use of oral anticoagulation current at time of randomisation (that is, up to three months before randomisation; yes or no), and whether patients were recruited from practices where one or more than one GP participated in the study.

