### Statistical analysis

All outcomes will be analysed according to the intention-to-treat principle, where patients are analysed according to the arm to which their practice cluster was allocated. Analyses of the outcomes will be implemented using marginal logistic regression models using generalised estimating equations (GEEs), with information sandwich ('robust) estimates of standard error to allow for within-cluster (within-general practice) correlation for dichotomous outcomes [40]. An exchangeable correlation structure will be specified for the marginal models using GEEs. Clustering will be accounted for only at the practice level as this is the unit of randomisation. Analyses will adjust for stratification of GPs by LGA.

In addition to unadjusted analyses, we will carry out adjusted analyses to allow for the effect of characteristics, current at the time of randomisation, as noted above.

Percentage of inter- and intrarater agreement and kappa coefficients will be calculated to quantify rates of reliability for the collected audit data [41].

Significance of the study results, specifically, the effect of the intervention on primary and secondary outcomes, will be ascertained by examining the magnitude of the estimated effect of the intervention and corresponding 95% CIs. When testing for interaction terms, a *p *value of < .05 will be used to determine significance of the effect. Analyses will be carried out blinded to group allocation.

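### Bleeding history up to randomisation is collected, but it is left out of the baseline comparison and, on the natural reading, out of the adjusted bleeding analyses

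*Protocol article*

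**What the plan says.** Under Cerebrovascular and bleeding events, the protocol article states that "All entries of cerebrovascular and bleeding events or episodes noted in the medical record from January 1, 2004 will be recorded". Two purposes are given: to identify new events in the 12 months after randomisation, and to establish "the history of these events current at the time of randomisation".

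Under Secondary outcomes, the adverse events include (b) major bleeding, (c) minor bleeding and (d) any bleeding. The last was added because it should have more events and be less sensitive to misclassification.

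The section on baseline comparisons gives an itemised list. It opens "Specifically, we will compare the DESPATCH and control groups on the numbers of patients identified with atrial fibrillation, patient sex, age", continues with "CHADS2 scores (0, 1, 2+, and mean scores), use of oral anticoagulation current at time of randomisation", and ends with "whether patients were recruited from practices where one or more than one GP participated in the study". Bleeding history is not on it.

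Under Statistical analysis, outcomes are analysed by logistic GEE with robust standard errors, clustered by practice and adjusted for Local Government Area (LGA). Beyond the unadjusted results, "we will carry out adjusted analyses to allow for the effect of characteristics, current at the time of randomisation, as noted above".

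**The concern.** The primary outcome has its baseline counterpart on the list, namely anticoagulation current at randomisation. Past stroke or TIA enters through CHADS2. Bleeding supplies three of the four lettered adverse-event outcomes and has no counterpart, although the history is gathered with that point in time in mind.

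The intervention aims to raise anticoagulant use, so readers will look closely at bleeding. Randomisation was by practice, stratified by LGA and ranked by practice size, and neither controls bleeding history. If the arms happened to differ in past bleeding, the planned baseline comparison would not reveal it and the adjusted models would not take it into account. Precision that is available from data in hand would also be given up, though only a little.

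**Working it through.** **Step 1. Trace the variable through the text.**

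| Section | Bleeding history |
|---|---|
| Cerebrovascular and bleeding events | Collected from 1 January 2004 (audited patients only; refusals excluded) |
| Baseline comparisons | Not listed |
| CHADS2 definition (Background) | Items are heart failure, hypertension, age over 75, diabetes, and stroke or TIA. A past haemorrhagic stroke could at most be counted under stroke; other bleeding has no route in |
| Statistical analysis | LGA, plus characteristics already noted |
| Secondary outcomes | Arms compared on (b), (c) and (d) |

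**Step 2. Reproduce the plan's own figures.** The plan gives no figure for bleeding. Its sample size supplies the cluster size and numbers used below.

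- 60% against 50%, two-sided 5%, 80% power: 388 per group without and 408 with continuity correction (stated: 407).
- Design effect: 1 + 24 × 0.04 = 1.96; 407 × 1.96 = 797.7, so 798.
- 798 / 0.9 = 887; 887 / 25 = 35.5, so 36 practices; 36 / 0.9 = 40 practices per group; 40 × 25 = 1,000 patients per group.

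The chain holds, and nothing in it depends on the present point.

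**Step 3. Size of the effect, under assumptions.** From the plan: 1,000 patients per arm, 25 per practice. Assumed, because the document gives no values: 12-month risk of any bleeding 15%; proportion with past bleeding p = 10% to 30%; risk ratio for past bleeding RR = 1.5 to 3; intracluster correlation (ICC) 0.01 to 0.10, the same for history and outcome.

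- D = 1 + 24 × ICC
- SD of the imbalance between arms = √(2p(1−p)D/1000)
- Risk without history r0 = 0.15 / (1 + p(RR−1)); with history r1 = RR × r0
- Shift in the crude risk difference when the imbalance is at its 95% limit = 1.96 × SD × (r1−r0)
- Standard error (SE) of the risk difference = √(2 × 0.15 × 0.85 × D/1000)
- R² = p(1−p)(r1−r0)² / (0.15 × 0.85); SE reduction = 1 − √(1−R²)

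| ICC, p, RR | 95% limit of imbalance | Shift | SE | Shift / SE | SE reduction |
|---|---|---|---|---|---|
| 0.01, 10%, 1.5 | 2.9 points | 0.21 points | 1.78 points | 0.12 | 0.2% |
| 0.04, 20%, 2 | 4.9 points | 0.61 points | 2.24 points | 0.27 | 1.0% |
| 0.10, 30%, 3 | 7.4 points | 1.39 points | 2.94 points | 0.47 | 2.9% |

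Substituting the formulas, shift / SE = 1.96 × √R². The design effect and sample size cancel, so the ratio depends only on how strongly past bleeding predicts new bleeding. Here √R² runs from about 0.06 to 0.24.

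**Step 4. Can major bleeding carry another covariate?** The Background cites a primary-care trial of warfarin against aspirin in elderly patients, with major haemorrhage at 1.9% and 2.0% per year. Taking 2% as an assumption, 2,000 × 0.02 = 40 events. The existing adjustment uses about 13 parameters: arm 1, LGA 6 (seven areas), sex 1, age 1, CHADS2 2, baseline anticoagulation 1, practice type 1. That is 40 / 13, or about 3 events per parameter, before anything is added.

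**The case against.** **Nothing here biases the comparison.** Patients were identified before practices were randomised, so the unadjusted bleeding comparison is unbiased in expectation. The cluster-robust interval already reflects chance imbalance, and the plan judges effects by their size and interval. This stands. A reader might infer that a bleeding difference in this trial could not be trusted; the document does not support that.

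**The adjustment set may be wider than the list.** The Statistical analysis section and the section on bleeding events both speak of what is current at randomisation, so a generous reading could bring bleeding history in. It is possible but unlikely, given the itemised list in between. Even then, the history would still be absent from the baseline comparison.

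**An article condenses, and covariates for secondary outcomes often go to the analysis plan.** That is fair in general. Here, however, the article sets out an itemised list and leaves out a variable that it collects.

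**A gain in power is tempting to claim.** Applying a 1 − ρ² variance factor to 80% power would suggest one. But that 80% belongs to 60% against 50% anticoagulation, no bleeding outcome has a stated power, and the factor is for a linear model whereas the plan uses logistic GEE. No power figure follows.

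**Past bleeding is not quite the same measure as the outcome.** The history spans January 2004 to October 2009 and the outcome 12 months. It is a prognostic history, not a like-for-like baseline value. The survey finding that GPs were cautious "even where treatment benefits clearly outweighed the risk of harm" concerns perceived risk, so it does not show that a patient's own recorded bleeding drives treatment.

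**Conclusion.** The point holds in a limited form. Bleeding history at randomisation is collected, is missing from the baseline list, and on the natural reading is missing from the adjustment set, although the arms are compared on bleeding. What is lost is visibility of a chance imbalance, the chance to adjust for it, and a little precision.

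Under the assumptions in the working, the arms could differ in past bleeding by about 3 to 7 percentage points (95% limits). The resulting shift in the risk difference is about 0.2 to 1.4 points, at most about half a standard error, and adjustment would shorten the standard error by about 0.2% to 3%. These figures are a linear approximation. They would be larger if past bleeding predicted new bleeding more strongly than assumed, and the shift would be larger relative to the standard error if past bleeding clustered more within practices than the outcome does. This is a worthwhile, inexpensive improvement. It does not invalidate the planned analysis.

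**What to change.** 1. Add bleeding recorded from 1 January 2004 to the date of randomisation (any; major) to the list under Baseline comparisons.
2. Under Statistical analysis, name past bleeding of any kind (yes/no) as a covariate in the adjusted model for outcome (d), any bleeding, and for (c), minor bleeding, if events allow. Report the result beside the unadjusted one.
3. Do not require it for (b), major bleeding, where sparse events could make the model unstable.
4. Replace the backward reference in the adjustment sentence with an explicit list of covariates.

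The cost is one extra derived covariate and no new data collection. The article says that data collection is still under way and that allocation codes are released only after the database is locked, so the change can be made before anyone analysing the data has those codes.

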## Demographic characteristics

Sex and year of birth will be documented.

## Primary outcome

We have defined the primary outcome as the proportion of patients with atrial fibrillation over the age of 65 years noted to be on treatment with oral anticoagulation at two prespecified time periods: (1) at *any *time in the 12 months from the date of randomisation and (2) currently (as defined below). Medical record notations of oral anticoagulant treatment, including prescriptions, consultation notes, referral letters, correspondence from specialists, hospital discharge summaries, and dates of INR results (with INR levels greater than 1.2), will be considered to be an indication that the patient is receiving anticoagulation on the date of the notation.

Anticoagulation indicated in the last three months of the 12-month period from randomisation will be considered 'current' if there is no noted suspension of warfarin or if a suspension is noted to be temporary. Three months is chosen as current to ensure adequate ascertainment of our anticoagulation indicators, such as doctor's follow-up notations, prescriptions, and correspondence.

At the time the study was devised and at the time of writing, warfarin was the only locally approved anticoagulant for the management of atrial fibrillation. During the study period, two fixed-dose oral anticoagulants (dabigatran and rivaroxaban) [33,34] had been under investigation in randomised controlled trials. Therefore, in addition to warfarin, these two treatments will also be considered as oral anticoagulant treatment in the unlikely event that patients in this project are receiving the drugs in trials or are receiving these treatments off-label. Other types of anticoagulation, such as clexane (enoxaparin) and heparin, will not be considered in our primary or secondary outcome assessment. These medications are not administered orally and are not usually indicated for long-term anticoagulation in NVAF.

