**Methods:**

DESPATCH is a cluster randomised controlled trial with concealed allocation and blinded outcome assessment designed to evaluate a multifaceted and tailored implementation strategy for improving the uptake of anticoagulation in primary care. We have recruited general practices in South Western Sydney, Australia, and randomly allocated practices to receive the DESPATCH intervention or evidence-based guidelines (control). The intervention comprises specialist decisional support via written feedback about patient-specific cases, three academic detailing sessions (delivered via telephone), practice resources, and evidence-based information. Data for outcome assessment will be obtained from a blinded, independent medical record audit. Our primary endpoint is the proportion of nonvalvular atrial fibrillation patients, over 65 years of age, receiving oral anticoagulation at any time during the 12-month posttest period.

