We set out to develop and evaluate a multifaceted, educational intervention (DESPATCH) tailored to the self-identified needs of Australian GPs, recognising their high perceived risk of anticoagulant use and the likely value of building confidence in decision making. The intervention features peer academic detailing and educational and practice materials. A novel element is expert decisional support to promote the uptake of anticoagulation, using feedback from clinical experts in stroke medicine.

Our primary hypothesis is that a higher proportion of patients with NVAF whose GPs have been randomly allocated to receive the DESPATCH intervention will be prescribed oral anticoagulation medication compared with patients whose GPs are allocated to the control group.

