### Subgroup analyses

For our primary outcome, we will carry out subgroup analyses, testing for interaction effects between four variables and trial arm status: (1) CHADS2 scores, (2) patient age (65 to 74 years, 75 to 84 years, and 85+ years), (3) recorded use of oral anticoagulation current at time of randomisation (that is, within three months of randomisation; yes or no), and (4) patient sex.

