### Sample size

Our sample size estimate was powered to detect a clinically important difference between groups for our primary outcome. We considered a 10% difference in the primary outcome to be clinically important. We assumed that 50% of patients with atrial fibrillation managed by GPs assigned to the control arm received anticoagulation; assuming a 50% use of anticoagulation in the control arm will produce a conservative (*i.e*., larger) sample size estimate. To detect a difference of 10% (*e.g*., 60% vs. 50%) in the primary outcome between intervention and control groups, with 80% power at the 5% level of significance, we would require 407 eligible patients per group in a trial in which the unit of randomisation is the patient [36].

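### The Abstract names one primary endpoint, the Methods define two, and the single 5% sample-size test does not say which it covers

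*Protocol article*

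**What the plan says.** - **Abstract, Methods.** One primary endpoint: the proportion of patients over 65 with nonvalvular atrial fibrillation "receiving oral anticoagulation at any time during the 12-month posttest period".
- **Primary outcome.** The proportion "noted to be on treatment with oral anticoagulation at two prespecified time periods", the first being any time in the 12 months from randomisation and the second being current use. On the second: "Anticoagulation indicated in the last three months of the 12-month period from randomisation will be considered 'current", provided that no lasting suspension is noted.
- **Primary hypothesis** (end of the section on previous studies). A higher proportion in the intervention arm "will be prescribed oral anticoagulation medication compared with patients whose GPs are allocated to the control group". No period is named.
- **Sample size.** "Our sample size estimate was powered to detect a clinically important difference between groups for our primary outcome". There is one calculation, "To detect a difference of 10% (*e.g*., 60% vs. 50%) in the primary outcome between intervention and control groups", made at a single 5% level for 80% power. Again no period is named.
- **Subgroup analyses.** "For our primary outcome, we will carry out subgroup analyses, testing for interaction effects between four variables and trial arm status", in the singular.
- **Statistical analysis.** Primary and secondary outcomes are judged by the size of the effect and its 95% confidence interval. A p-value threshold (.05) is given only for interaction terms. The two periods are not ranked, and no joint requirement or adjustment is stated.

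**The concern.** Any-time use and current use are different binary variables. A patient treated in month 2 and then permanently stopped is a success on the first and a failure on the second. The article's own background shows that this matters: in the decision-aid trial it describes, prescribing rose at three months and was back at baseline by 12 months. A similar transient effect here could be positive on any-time use and null on current use, and the document would not say whether the trial had succeeded.

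Two things are at stake. The first is which result decides the trial, since a reader checking the final report against this article would find support for either choice. The second is the error rate. If a favourable 95% interval for either period were enough, two 5% tests would stand where the sample size provides for one.

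**Working it through.** **Step 1. Reproduce the planned size.** Inputs from the Sample size section: 50% v 60%, 5% significance (taken as two-sided), 80% power. With mean proportion 0.55:

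n = [1.960 × √(2 × 0.55 × 0.45) + 0.842 × √(0.50 × 0.50 + 0.60 × 0.40)]² / 0.10² = 387.3

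With continuity correction: n′ = (n/4) × [1 + √(1 + 4/(n × 0.10))]² = 407.1, which matches the stated 407. The rest follows:
- design effect 1 + 24 × 0.04 = 1.96, and 407 × 1.96 = 797.7 (798);
- 798/0.9 = 886.7 (887);
- 887/25 = 35.5 (36 practices), and 36/0.9 = 40 practices per group.

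So the plan sizes exactly one two-sided 5% test.

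**Step 2. Correlation of the two outcomes.** Current use is nested within any-time use. For nested binary outcomes with proportions a (any time) and c (current), the correlation is √[c(1 − a) / (a(1 − c))]. The document gives only a 50% control rate, for an unspecified period. I take a = 0.50 and assume c between 0.35 and 0.45. This patient-level correlation is used as an approximation for the correlation of the two test statistics.

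**Step 3. Chance of at least one false positive if either period may count alone.** This is P(|Z1| > 1.96 or |Z2| > 1.96) under a bivariate normal:

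| Any-time use | Current use | Correlation | At least one false positive |
|---|---|---|---|
| 50% | 35% | 0.73 | 8.2% |
| 50% | 40% | 0.82 | 7.7% |
| 50% | 45% | 0.90 | 7.0% |

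The upper limit, for independent tests, is 1 − 0.95² = 9.75%. If both periods had to be significant, the rate could not exceed 5%.

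**Step 4. What each way of keeping both would cost.**
- *Split at 2.5% each.* Power at the planned size is Φ[(0.10 × √387.2 − 2.241 × 0.7036)/0.70] = 71%, where 387.2 is the uncorrected equivalent of 407. Restoring 80% needs 489 per group before clustering. Then 489 × 1.96 = 958.4 (959), 959/0.9 = 1,065.6 (about 1,065 if not rounded at each step), 1,065/25 = 42.6 (43 practices) and 43/0.9 = 47.8 (48 practices per group), against the planned 40.
- *Both required.* If each period alone has 80% power, joint power is the bivariate normal probability with both limits at 0.84: 72% at correlation 0.73 and 75% at 0.90.
- *One period named as primary.* No change to 407, 798, 887 or 40.

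**Step 5. Interaction tests.** Four independent tests at .05 give 1 − 0.95⁴ = 18.5%. Running the four variables on both periods, with the Step 3 rates, gives 1 − (1 − 0.0818)⁴ = 28.9% down to 1 − (1 − 0.0699)⁴ = 25.2%.

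**The case against.** The strongest reply is that the document never says either period alone is enough. Results are to be read from effect sizes and intervals, not from a declared success rule. Multiplicity methods and the reading of split results are commonly left to a statistical analysis plan, which is not shown here. That stands, so the 7% to 8% can only be conditional. It does not remove the conflict between the Abstract and the Primary outcome section, which lies within this one document and concerns what the primary outcome is.

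Three stronger readings are tempting and are not supported:
- A reader might infer that the sample size gives each period its own 5% test. It does not. It holds one calculation at one 5% level and leaves the period unnamed.
- A reader might infer that the subgroup plan amounts to eight independent tests with a 34% chance of a false positive (1 − 0.95⁸). The section lists four variables for a primary outcome in the singular. Even if both periods were tested, their correlation brings the figure down to about 25% to 29%, and 18.5% would remain with four.
- A reader might infer that current use should be the primary outcome. Nothing in this point requires that. The Abstract's endpoint is any-time use, which the Methods also list first.

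**Conclusion.** The conflict is real and can be shown from the article alone: one primary endpoint in the Abstract, two in the Methods, and one 5% sample-size test tied to neither. Nothing in the article says which period decides.

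That the trial has two chances to claim success is something a reader might infer, not something the document states. It holds only if either period may count alone. In that case the familywise error would be about 7% to 8%, with a ceiling of 9.75%. With both required there is no inflation, but joint power falls below 80%. The 7% to 8% rests on the assumed 50% any-time and 35% to 45% current use and on the normal approximation. The contradiction rests on no assumption.

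**What to change.** Before group codes are released, reconcile the Abstract, the Primary outcome section and the Sample size section:

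1. Name one period as the single primary outcome and make the other secondary. The Abstract's period is any-time use. The choice belongs to the investigators, and either choice cures the defect. State in the Sample size section that the calculation is for that period.
2. If both are to stay primary, say so in the Abstract. Then state either that both must be significant, or that Hochberg's procedure is applied at an overall 5%, and restate the power for the rule chosen.
3. Run the four interaction tests on the single primary outcome only.

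Under the first option the sample size does not change. It is still a decision about which result counts, so it should be dated and recorded before unblinding. The article reports that data collection has begun but is not complete, and that group codes are released only after the database is locked, so there is time. The price is that the other period's result can no longer be headlined alone.
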